### Relevant concomitant care permitted or prohibited during the trial {11d}

All procedures, interventions, and medications required for optimal patient treatment are allowed during the study. Any medications administered or additional interventions required during the trial will be documented on the case report form. All procedures, interventions, and medications administered in this study adhere to established internal standard procedures and clinical protocols. Potential side effects primarily include hemodynamic or respiratory complications. However, to mitigate these risks, each patient will be under the direct supervision of a board-certified anesthesiologist with extensive experience in managing such complications during surgical procedures. Consequently, we assess the likelihood of experiencing adverse events as low. Detailed information regarding possible adverse events is provided in Item 22. Additionally, as stated in Item 30, patient insurance coverage is available to address any adverse events should they occur.

### Provisions for post-trial care {30}

A patient insurance with an insurance number of maximum 5,000,000 Euro (maximum 500,000 Euro per participant) exists with HDI Global SE (99.9%) and HDI-Haftpflichtverband der Deutschen Industrie V.a.G. (0.1%) if study-associated complications should occur. The monitoring period ends after discharge from the recovery room. Further follow-up is not required.

### Outcomes {12}

The primary endpoint of this trial is the difference in driving pressure (ΔP) between the intervention and control group during general anesthesia in endotracheal intubation and volume-controlled ventilation (VCV). Secondary endpoints include:

Mechanical Power of ventilation (elastic-dynamic, tidal and total).Compliance of the respiratory system.Intraoperative fluid requirements.Average intraoperative vasopressor requirements (µg/kg/min).Number of intraoperative hypotension events (MAD < 65 mmHg for > 1 min).Time-weighted average of hypotension.Number of alveolar recruitment maneuvers (to be performed if SpO_2_ < 90% with FiO_2_ > 60%).SpO_2_ after arrival in recovery room (without oxygen insufflation).Number of patients with indication for oxygen insufflation (to maintain SpO_2_ ≥ 90%).Change in lung aeration score between before surgery and after arrival in recovery room(determined by lung ultrasound).Overall postoperative pulmonary complications.

For further clarification see, Table 1 (“Outcome Definition”).

**Table 1 Tab1:** Outcome definition

**Domain**	Respiratory mechanics	Rescue therapy	Hemodynamics	Postoperative status
Specific measures	• Driving pressure • Mechanical power of ventilation (elastic-dynamic, tidal, and total) • Compliance of respiratory system	• Number of alveolar recruitment maneuvers	• Intraoperative fluid requirements • Average intraoperative vasopressor requirements • Number of intraoperative hypotension events • time-weighted average of hypotension	• SpO_2_ after arrival in recovery room • Number of patients with additional oxygen insufflation^a^ • Change in lung aeration score
Specific metric	Difference between control and intervention group	Difference between control and intervention group	Difference between control and intervention group	Difference between control and intervention group
Method of aggregation	Mean + SD (parametric data) or Median/IQR (non-parametric data)	Mean + SD (parametric data) or Median/IQR (non-parametric data)	Mean + SD (parametric data) or Median/IQR (non-parametric data)	Mean + SD (parametric data) or Median/IQR (non-parametric data) and four-square table^a^
Time point	Intraoperative	Intraoperative	Intraoperative	Postoperative

Outcomes are defined following the framework of Saldanha et al. [20]

^a^Four-square table is only used as method of aggregation for “number of patients with additional oxygen insufflation”

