### Trial design {8}

The BodyVent trial is a randomized, controlled, patient blinded single-center superiority trial with two parallel groups and a primary endpoint of driving pressure (ΔP) within volume-controlled ventilation in endotracheally intubated patients during general anesthesia. Randomization is performed by random permuted block randomization with a 1:1 allocation ratio.

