### Eligibility criteria {10}

To be eligible, patients must meet the following inclusion criteria: [1] Surgery under general anesthesia with endotracheal intubation is planned, [2] the expected duration of surgery exceeds 2 h, [3] participants are at least 18 years of age, and [4] written informed consent is obtained. Potential patients will be excluded if any of the following exclusion criteria are fulfilled: [1] planned intraoperative ventilation via a face mask or a laryngeal mask airway, [2] laparoscopic surgery, thoracic surgery or surgery with cardiopulmonary bypass is planned, [3] surgery will be performed in > 10° Trendelenburg/Anti-Trendelenburg position, [4] pregnancy, [5] BMI > 60, [6] acute cardiac decompensation, [7] severe pre-existing pulmonary conditions (e.g., acute pulmonary decompensation, acute respiratory distress syndrome, pulmonary fibrosis, present pneumonia, chronic obstructive pulmonary disease severity GOLD IV), [8] inability to give informed consent.

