### Sample size {14}

Sample size calculation was performed with G*power 3.1 Software [13]. Assuming a mean (± SD) ΔP of 10 (± 3) mbar at PEEP = 5 mbar and a mean ΔP of 8 (± 2) mbar at PEEP = BMI/3 mbar, *α* = 0.05, 1 − *β* = 0.8, G*Power yielded a required sample size of *n* = 54 (27 per group) patients. The anticipated effect size is based on the results previously published by Pereira et al. [10]. To compensate for refusal, technical difficulties, or possible dropouts, we will increase the sample size by 10%, resulting in a total sample size of 60 patients.

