## Statistical methods

### Statistical methods for primary and secondary outcomes {20a}

The primary objective of the study is to determine whether BMI-adjusted ventilation strategies result in a reduction of driving pressure. Data are tested for normal distribution using the Shapiro–Wilk test. Differences between the intervention group and the control group are assessed with a two-tailed unpaired *t*-test for normally distributed continuous data and with the Mann–Whitney test for non-normally distributed continuous data. In addition, descriptive statistical analyses (mean ± standard deviation, median, interquartile range, and 95% confidence interval, if applicable) will be performed.

For secondary endpoints, to evaluate the changes in lung ultrasound score between the pre- and postoperative groups and between the intervention groups, a two-way ANOVA will be performed with the time point (preoperative/postoperative) as one independent variable and the study group (intervention/control) as the other independent variable. For categorical variables (hypotension events, number of patients requiring supplemental oxygen), Fisher’s exact test will be used. For the secondary endpoint “time-weighted average of hypotension events,” the area under the threshold of 65 mmHg (AUC) for each event will be calculated by summing the difference between MAP and the threshold, multiplied by the duration of the event. Total AUC will be divided by the observed time, which varies by patient. This results in a time-weighted average of hypotension per patient.

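### Hypotension events and recruitment manoeuvres are counted per patient without allowance for observation time, and the hypotension count is then reduced to a categorical test: a minor loss of precision on secondary endpoints

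*Protocol article*

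**What the plan says.** All references are to the protocol article.

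- **Outcomes {12} and Table 1.** Five intraoperative secondary endpoints depend on how long the patient is observed. Vasopressor use is given per kg per minute, and hypotension burden is a time-weighted average. The other three have no denominator: the number of hypotension events, the number of recruitment manoeuvres, and "Intraoperative fluid requirements", for which no unit is given at all. Table 1 summarises all five by mean and SD or median and IQR. Its footnote reserves the four-square table for supplemental oxygen alone.
- **Statistical methods {20a}.** For the hypotension area the text says "Total AUC will be divided by the observed time, which varies by patient". Hypotension events are classed as categorical, together with the number of patients needing oxygen, and go to Fisher's exact test. Manoeuvres and fluid have no test of their own, so the general rule (t-test or Mann–Whitney) would apply.
- **Eligibility criteria {10}.** The only limit on duration is a lower one: "the expected duration of surgery exceeds 2 h".
- **Intervention description {11a}.** Manoeuvres have two triggers, circuit disconnection and desaturation. The outcome list mentions only desaturation.

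**The concern.** The article recognises that observed time differs between patients and corrects for it in two of the five exposure-dependent endpoints, but says nothing of it for the other three. A patient observed for twice as long has about twice the opportunity to have an event.

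Hypotension events have a second problem. They are defined as a count and summarised as a count, but tested as a category. The categories are not stated; any event against none is the natural reading. That test cannot separate one episode from six. It has little left to compare if most patients have at least one episode, and whether a patient has any episode itself depends on duration.

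The Discussion names safety among the aims, and these endpoints bear on it. A weak test makes a real difference easier to miss, and a null result could then be read as reassurance.

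**Working it through.** **1. The plan's own figure.** The inputs from Sample size {14} are "ΔP of 10 (± 3) mbar at PEEP = 5 mbar" and "mean ΔP of 8 (± 2) mbar at PEEP = BMI/3 mbar", with α = 0.05 and power 0.80. The test is "two-tailed unpaired" ({20a}) and allocation is 1:1 ({8}).

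- SD = √((3² + 2²)/2) = 2.55, and d = 2/2.55 = 0.784.
- The exact noncentral t calculation gives 27 per arm, 54 in all, with power 0.8075.
- 54 × 1.10 = 59.4 and 54/0.90 = 60, so both rules lead to the stated 60.

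The sample size reproduces. It concerns driving pressure only and is not affected by this point.

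**2. Assumptions.** The documents give no spread for operating time, fluid or event rates. Assumed: CV of duration 0.3–0.6, CV of hourly fluid rate 0.3–0.6, event rates 0.1–1.0 per hour, and median duration 3–3.5 h.

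**3. Any-event status depends on duration and saturates.** With Poisson events at rate λ per hour over T hours, P(any event) = 1 − exp(−λT). The case T = 7 h is twice the assumed median.

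| T | λ = 0.5/h | λ = 1.0/h | difference |
|---|---|---|---|
| 2 h | 0.63 | 0.86 | 0.23 |
| 3.5 h | 0.83 | 0.97 | 0.14 |
| 7 h | 0.97 | 1.00 | 0.03 |

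The rate is doubled in every row, yet the contrast visible to Fisher's test shrinks from 23 to 3 percentage points. Differences between patients in their underlying rate soften this but do not remove it.

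**4. Power for hypotension events.** Simulated with doubled rate, 30 per arm, gamma-Poisson counts, base rate 0.5 per hour and duration CV 30–60%:

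- Fisher on any event: 0.17–0.20
- Mann–Whitney on raw counts: 0.61–0.68
- rate comparison with log-time offset: 0.76–0.78

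At a base rate of 1 per hour, Fisher falls to about 0.06–0.07. Most of the gain comes from keeping the count; the offset adds roughly 0.1 more. A small part of that last step may not be true gain, because a quasi-Poisson test at this sample size can exceed its nominal 5% slightly when durations are very uneven.

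**5. What dividing a count by time does to its variance.** The squared CV of the total, relative to that of the total per hour, is 1.07–1.58 at 0.5–1 event per hour but 0.88–0.98 at 0.1 per hour. For rare events, simple division gains nothing and adds slight noise. An offset model avoids the division.

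**6. Fluid, if it were compared as a total.** If volume is rate × time, with the two independent, CV²(total) = (1 + CV²(rate))(1 + CV²(time)) − 1. With rate CV 0.4:

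- duration CV 0.3: 1.16 × 1.09 − 1 = 0.264, which is 1.65 times the rate's 0.16
- duration CV 0.6: 1.16 × 1.36 − 1 = 0.578, which is 3.6 times

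Over the whole assumed grid the ratio is 1.3–5.4. For a 35% difference with 30 per arm and rate CV 0.4, power is about 0.82 per hour. On totals it is about 0.61, 0.47 and 0.36 at duration CV 30, 45 and 60%. If a fixed part worth 2 h of infusion is added, the contrast narrows to 0.78, 0.77 and 0.74 per hour against 0.73, 0.63 and 0.53.

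**7. Chance imbalance.** With 27 per arm, the standard error of the between-arm difference in mean duration is CV × √(2/27). That is 8.2% of the mean at CV 0.3 and 16.3% at CV 0.6.

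**The case against.** A reader might infer that fluid, hypotension events and manoeuvres are all compared as raw totals. The documents do not support that. Hypotension events go to a categorical test. Fluid merely lacks a unit, and an article may leave that to the full protocol or analysis plan. Only the manoeuvre count is plainly a number per patient, and those after disconnection need not scale with time. This part of the objection stands.

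A reader might also infer bias, or that totals mainly reflect how long the operation lasted. Neither follows. Randomisation balances duration on average, leaving only precision and chance imbalance. With duration CV 30% and rate CV 40%, duration supplies ln 1.09/(ln 1.09 + ln 1.16) = 0.086/0.235, or about 37% of the log-variance of a proportional total.

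Two of the four haemodynamic measures are already time-standardised, so the haemodynamic question does not rest on the counts alone. The section on the data monitoring committee {21a} also calls the trial a pilot that is not powered for patient-centred outcomes. Both points limit the consequence.

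Finally, {11b} discontinues the intervention when hypotension needs treatment, so observed time is not the same as time on the assigned PEEP. That is true, but it applies equally to the time-weighted average that the plan already uses.

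What remains is what the article itself fixes: a count endpoint tested as a category, contrary to its own Table 1, and two counts with no allowance for a time that it says varies.

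**Conclusion.** The point holds as a minor matter of precision on secondary endpoints. The primary endpoint and the sample size are untouched, and there is no systematic bias.

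The firmest part is the hypotension count. Fisher's test discards most of the information: under the stated assumptions, power for a doubled rate is about 0.2, against 0.76–0.78 for a rate model. The gain for manoeuvres is small in absolute terms if they are rare. For fluid the gain could be material, but only if the intention is to compare total volume, which is an inference, and it shrinks if volume is only partly proportional to time.

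Every size given here depends on assumed event rates, spreads and differences between patients. The direction for the hypotension count does not need those exact values, provided that events are not very rare.

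**What to change.** - **Hypotension events:** analyse the number per patient with a negative binomial or quasi-Poisson model, with log(observed time) as offset, and report a rate ratio with its 95% confidence interval. Define observed time once and use the same definition as for the time-weighted average. Keep the raw counts and Fisher's test as description, and state the categories.
- **Manoeuvres:** count those triggered by desaturation separately from those after disconnection. Use the same model for the former and describe the latter.
- **Fluid:** state the unit and report it per hour, in line with the vasopressor endpoint. If it is also scaled by weight, say whether actual or predicted weight is used. The choice matters in a trial that admits BMI up to 60 and uses predicted weight for tidal volume.

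The cost is a few lines of analysis wording. Observed time is already needed for the time-weighted average, and weight is measured after consent. The one small downside is that the count model is less stable when events are very rare; a prespecified fallback, such as a permutation test of the rate ratio, would cover that and the slight excess over the nominal 5%. If outcome data by group have already been examined, label the rate analyses as post hoc.

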### Participant timeline {13}

Within the week before surgery, patients will visit the pre-medication outpatient clinic. Participants will be screened and, if eligible, will be asked to provide written informed consent to participate in the study. Only patients who provide consent will be included in the study. After obtaining consent, total height, weight, and waist to hip ratio will be measured. On the day of surgery, a preoperative lung ultrasound examination will be carried out immediately before the patient is admitted to the operating room. After induction of general anesthesia, patients will be randomized by opening a sealed envelope. The protocol is then carried out accordingly for the control group or for the intervention group. After extubation, patients will be transferred to the recovery room. A postoperative lung ultrasound examination will be carried out. Additional oxygen will be applied if oxygen saturation drops below 90% breathing room air. Patients will be discharged from the recovery room according to routine clinical criteria (oxygen saturation > 90% or similar to preoperative value breathing room air, hemodynamic stability, patient awake and oriented, sufficient pain control). Data collection ends after patient is discharged; no further follow-up is needed (Fig. 2).

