### Methods in analysis to handle protocol non-adherence and any statistical methods to handle missing data {20c}

If the protocol could not be completely adhered to, or individual data is missing, a drop-out rate of 10% was considered in the sample size calculation. A per-protocol analysis will be performed with respect to the study intervention (PEEP setting). Data sets will only be excluded from the per-protocol analysis if the study intervention (PEEP setting) was not performed, or if the primary endpoint (ΔP) cannot be evaluated. For all other endpoints, if there are missing values, the number of missing values will be reported in the manuscript and analyses will be performed as planned.

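### Recovery-room room-air SpO2 is compared as an unadjusted absolute value although the plan already relies on a preoperative saturation; adjusting for it would gain precision at almost no cost

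*Protocol article*

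**What the plan says.** **Endpoint.** Outcomes {12} of the protocol article lists, as one of eleven secondary endpoints, SpO2 "after arrival in recovery room (without oxygen insufflation"). Table 1 places it under postoperative status, with a difference between the two groups as the metric. It has no preoperative reference.

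**Analysis.** Section 20a tests continuous data for normality, then compares groups with an unpaired t-test or a Mann–Whitney test. No covariate is named, and section 20b plans no further analyses.

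**Missing values.** For endpoints other than the primary, section 20c states that "the number of missing values will be reported in the manuscript and analyses will be performed as planned".

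**Preoperative reference used elsewhere.** Participant timeline {13} accepts, as one way of meeting the saturation criterion for discharge, a value "similar to preoperative value breathing room air". The abstract can be read as saying that respiratory vital signs are recorded both before and after surgery. The lung ultrasound endpoint is a within-patient comparison: "Change in lung aeration score between before surgery and after arrival in recovery room".

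**Companion endpoint.** The plan also counts the "Number of patients with indication for oxygen insufflation" needed to keep SpO2 at or above 90%. Section 13 has the matching care rule: "Additional oxygen will be applied if oxygen saturation drops below 90% breathing room air".

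**The concern.** A saturation measured in the recovery room reflects both what happened during anesthesia and what the patient's saturation usually is. Eligibility {10} sets no saturation limit. It admits BMI up to 60, and the one COPD stage it names among its examples of severe lung disease is "chronic obstructive pulmonary disease severity GOLD IV". Usual room-air values may therefore vary between patients for reasons unrelated to PEEP.

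The plan recognises this in its discharge criterion and handles the same issue for lung ultrasound by measuring before and after. For SpO2 it fixes an analysis that ignores the preoperative value. With about 30 patients per arm, that leaves noise in the trial's one continuous measure of postoperative oxygenation. A modest real difference is then harder to see, and a chance imbalance in baseline saturation goes uncorrected.

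**Working it through.** **1. The plan's own figure.** The documents give no assumed mean, SD or power for SpO2. The only calculated figure is the sample size for driving pressure, and it reproduces. The pooled SD is √((3² + 2²)/2) = 2.55, so d = 2/2.55 = 0.784. A two-sided t-test at α = 0.05 with 80% power needs 26.5, rounded up to 27 per group, or 54 in total; 54/0.9 = 60. This has no bearing on the SpO2 point beyond giving n = 60/2 = 30 per arm.

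**2. Inputs for the SpO2 comparison.**
- n = 30 per arm (Sample size {14}, 1:1 allocation).
- σ = SD of recovery-room SpO2. It is not stated and cancels from the ratios below.
- r = correlation between preoperative and recovery-room room-air SpO2. It is not stated; 0.3 to 0.7 is assumed.

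**3. Formulas.**
- Unadjusted: SE = σ√(2/30) = 0.258σ.
- Change from baseline: variance multiplied by 2 − 2r.
- Adjusted for baseline (ANCOVA): variance multiplied by 1 − r², ignoring the one degree of freedom spent on the covariate.

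**4. Results.**

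| r | Change-score variance factor | ANCOVA variance factor | Variance removed by ANCOVA | ANCOVA SE | Unadjusted n per arm giving the same precision |
|---|---|---|---|---|---|
| 0.3 | 1.40 | 0.91 | 9% | 0.246σ | 30/0.91 = 33 |
| 0.5 | 1.00 | 0.75 | 25% | 0.224σ | 30/0.75 = 40 |
| 0.7 | 0.60 | 0.51 | 49% | 0.184σ | 30/0.51 = 59 |

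Adjustment gains over the whole range. A simple change score is worse than the unadjusted comparison when r is below 0.5, so adjustment is the better use of the baseline.

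**5. Missing values.** Under section 13, extubated patients go to the recovery room and oxygen starts when room-air saturation falls below 90%. A patient on that path has a room-air value before oxygen begins. A patient who arrives on oxygen that cannot be withdrawn, or who stays ventilated, has none. Section 20c gives no substitute for a missing value, so such a patient would not enter the SpO2 comparison. The documents do not say how many there would be.

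**The case against.** **Absolute endpoints are legitimate in a randomized trial.** This stands. With 1:1 allocation, pre-existing low saturation is balanced in expectation. A reader might infer that chronic hypoxaemia biases the comparison, but it adds noise and possible chance imbalance, not systematic error. Severe lung disease is also excluded by a list of examples, so GOLD IV is not the whole of that exclusion, and no figure shows how many patients would have a low usual saturation.

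**The assumed correlation may be too high.** SpO2 is capped at 100%, and recovery-room values also reflect residual anesthesia. This is fair, and it is why the range starts at 0.3, where the gain is only 9%.

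**Nothing says that unmeasurable patients are dropped.** This also stands. A reader might infer that the worst outcomes systematically go missing. No section orders an exclusion, and patients who fall below 90% on room air have a value and also count in the oxygen endpoint. If, hypothetically, every value below 90% were lost, a true 1.0-point difference would appear as 0.58 to 0.92 (assumed control mean 92–94, SD 2–3), but the documents describe no such loss. What remains is narrower: no rule covers a patient who never has a room-air value. An article may leave that to a fuller document, so it supports a sensitivity analysis and no more.

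**The oxygen-need endpoint might seem to need the same correction.** A fixed 90% threshold does dilute a contrast. With assumed new oxygen need of 30% v 10%, and 5%, 10% or 15% of both arms already below 90%, the risk ratio falls from 3.0 to 2.3, 1.9 or 1.7. Fisher power at 30 per arm falls from 0.37 to 0.30, 0.25 or 0.21. But the endpoint matches the section 13 rule for giving oxygen. Requiring a value below the patient's own baseline as well would leave out patients who actually receive oxygen. With no margin, it would also let a one-point fluctuation decide the event. Nor does the sensitivity of Fisher's test to one patient (2 v 9 events, p = 0.042; 2 v 8, p = 0.080) show a fault here: 1 v 7 gives 0.052 and 1 v 8 gives 0.026. That is a property of any such test at this size.

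**Conclusion.** The point holds as a loss of precision on one secondary endpoint. The plan fixes an unadjusted comparison of recovery-room SpO2 while using a preoperative room-air saturation for discharge and a pre/post comparison for lung ultrasound. Adjustment would remove about 9% to 49% of the residual variance. That range rests entirely on the assumed correlation of 0.3 to 0.7. The stronger readings, that the comparison is biased or that the worst patients are excluded, are not supported by the text. The primary endpoint, its test and the sample size of 60 are unaffected.

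**What to change.** - **Section 20a:** compare recovery-room room-air SpO2 between arms adjusted for preoperative room-air SpO2, by ANCOVA, or by a rank-based version if the distribution is skewed.
- **Section 20c:** add a sensitivity analysis in which a patient with no room-air value, because oxygen or ventilation could not be withdrawn, receives the worst rank. Report the number of such patients by arm.
- **Oxygen-need endpoint:** leave the definition as it is. If wanted, report alongside it how many of the counted patients were already below 90% on room air before surgery.

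The cost is small. The preoperative room-air value must be entered on the case report form as a covariate, and a few lines of text change. Care does not change. Because the analysts of these data are not blinded, the adjusted analysis should be fixed before the arms are compared; otherwise it should be labelled post hoc.

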**Methods:**

Patients undergoing general anesthesia and endotracheal intubation with volume-controlled ventilation with a tidal volume of 7 ml per kg predicted body weight will be randomized and assigned to either an intervention group with PEEP adjusted according to BMI or a control group with a standardized PEEP of 5 mbar. Pre- and postoperatively, lung ultrasound will be performed to determine the lung aeration score, and hemodynamic and respiratory vital signs will be recorded for subsequent evaluation. The primary outcome is the difference in ΔP as a surrogate parameter for lung-protective ventilation. Secondary outcomes include change in lung aeration score, intraoperative occurrence of hemodynamic and respiratory events, oxygen requirements and postoperative pulmonary complications.

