Several previously conducted studies propose an association between high ΔP, high elastic-dynamic mechanical power (the product of ΔP, tidal volume, and respiratory rate) and unfavorable outcomes for patients with acute respiratory distress syndrome [17, 18]. For patients undergoing mechanical ventilation during general anesthesia, the available evidence suggests that a ventilation strategy that leads to a reduction in ΔP also reduces the risk of postoperative pulmonary complications [5]. For this reason, ΔP was chosen as primary endpoint in this trial. To further analyze the effect of PEEP adjustment according to BMI, respiratory system compliance, the different components of mechanical power (elastic-static, elastic-dynamic, resistive, total, tidal), intraoperative hemodynamics, postoperative oxygen requirements, and the number of intraoperative recruitment maneuvers required to maintain SpO_2_ > 90% with FiO_2_ < 60% will be recorded.

Available data suggest that 1 mbar increase in ΔP leads to a 16% relative risk increase for postoperative pulmonary complications (odds ratio for one unit increase of driving pressure 1.16) [5]. With an incidence of postoperative pulmonary complications around 5% in a mixed surgical population [1] and an assumed reduction of driving pressure by 1–2 mbar with PEEP adjusted according to BMI, a sample size of several thousand patients would be required to show a statistically significant reduction in postoperative pulmonary complications with our strategy. We therefore chose driving pressure as easy to measure and clinically relevant surrogate outcome parameter for our single-center trial assuming that a ventilation strategy that leads to a reduction in ΔP will ultimately reduce the risk of postoperative pulmonary complications in larger populations.

However, as this is the subject of the study, we cannot exclude with certainty that ΔP and the associated risk of postoperative pulmonary complications could also be increased with the ventilation strategy studied. Further limitations include that results may not be applicable to procedures with altered intrathoracic or intraabdominal pressures, such as laparoscopic or thoracic procedures or patient’s positions other than flat supine. Due to the study design the occurrence of PPCs could not be evaluated, this would have required a significantly higher number of patients. Thus, this aspect should be considered in further studies.

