In conclusion, the study results will show whether an intraoperative ventilation strategy with PEEP adjustment based on BMI has the potential of reducing the risk for postoperative pulmonary complications as an easy-to-implement intervention that does not require lengthy ventilator maneuvers nor additional equipment.

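### Overall postoperative pulmonary complications are a listed secondary outcome, but observation ends at recovery-room discharge and the Discussion says their occurrence could not be evaluated

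*Protocol article*

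**What the plan says.** In the protocol article, the last item in the list of secondary endpoints in Outcomes {12} is "Overall postoperative pulmonary complications". The Abstract (Methods) also ends its secondary outcomes with "oxygen requirements and postoperative pulmonary complications".

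Other sections point the other way:

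- **Provisions for post-trial care {30}:** "The monitoring period ends after discharge from the recovery room. Further follow-up is not required".
- **Participant timeline {13}**, directly after the recovery-room discharge criteria: "Data collection ends after patient is discharged; no further follow-up is needed".
- **Table 1**, to which Outcomes {12} refers for clarification: the postoperative column holds oxygen saturation, "Number of patients with additional oxygen insufflation" and change in lung aeration score. PPCs are the only listed secondary endpoint that is not in the table.
- **Objectives {7}:** PPCs are not among the secondary objectives.
- **Data monitoring committee {21a}:** the trial is described as a pilot without power for patient-centered outcomes.
- **Discussion:** "Due to the study design the occurrence of PPCs could not be evaluated, this would have required a significantly higher number of patients".

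**The concern.** A trial cannot both report PPCs as a secondary outcome and be unable to evaluate them. These are two statements in the current text, not a detail left to a fuller document.

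The observation window makes the conflict substantive. A patient leaves the recovery room once judged stable, including in respiratory terms, and recording stops there. Anything that appears later is lost in both arms. A count cut off at that moment is not a count of overall PPCs, whatever definition the full protocol may use.

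If the list is followed as written, the report must either publish a between-group PPC comparison that the authors say cannot be made or drop a listed outcome without explanation. In the first case, a reader could take similar or low counts as evidence that the strategy is safe or beneficial for the lung.

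**Working it through.** **Step 1. The window.** Eligibility {10} requires an expected duration of surgery above 2 h. The Discussion puts the usual recovery-room stay at half the operating time. So 0.5 × 2 h = 1 h, and observation typically lasts about an hour or somewhat more after surgery. PPCs after that point are not recorded ({13}, {30}).

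**Step 2. The trial size.** Sample size {14} assumes driving pressure of 10 (SD 3) versus 8 (SD 2) mbar, α = 0.05 and power 0.80. The test is two-sided ({20a}).

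- Common SD = √((3² + 2²)/2) = 2.55, so d = 2/2.55 = 0.784.
- The t-test calculation gives 26.5, hence 27 per group and 54 in total.
- 54 × 1.10 = 59.4, hence 60.

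The stated size reproduces, and it was set for driving pressure only.

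**Step 3. PPCs with full follow-up.** The Discussion gives an incidence of about 5%. With p = 0.05:

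- Expected events: 60 × 0.05 = 3.0 in total, or 1.5 per arm of 30.
- P(no event in 60) = 0.95^60 = 0.046.
- P(0 or 1 in 60) = 0.95^60 + 60 × 0.05 × 0.95^59 = 0.19.
- P(no event in one arm of 30) = 0.95^30 = 0.21.

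**Step 4. PPCs within the recovery room.** The documents do not say what share of PPCs appears before recovery-room discharge. It is treated here as an assumption, s, with event probability 0.05 × s per patient and N = 60:

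| Assumed share s | Expected events | P(0) | P(0 or 1) |
|---|---|---|---|
| 50% | 1.5 | 0.22 | 0.56 |
| 25% | 0.75 | 0.47 | 0.83 |
| 10% | 0.3 | 0.74 | 0.96 |
| 5% | 0.15 | 0.86 | 0.99 |

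A smaller share means fewer expected events and a larger chance of seeing none.

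**Step 5. What a low count could show.** For 0 events in 30 patients, the exact two-sided 95% upper limit is 1 − 0.025^(1/30) = 11.6%, more than twice the 5% background rate. For 0 in 60 it is 1 − 0.025^(1/60) = 6.0%, still above 5%. Even a zero count would not exclude the ordinary rate.

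**Step 6. The article's own estimate of the size needed.** The Discussion uses an odds ratio of 1.16 per mbar and a reduction of 1–2 mbar, and concludes that several thousand patients would be needed.

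- 2 mbar: odds = (0.05/0.95)/1.16² = 0.0391, so p₂ = 3.76%. At two-sided 0.05 and 80% power this needs about 8,600 patients.
- 1 mbar: p₂ = 4.34%, which needs about 32,100 patients.

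The article's statement fits the 2 mbar end. Either way, it already concedes that 60 patients cannot answer the PPC question.

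**The case against.** The strongest reply is that the article is open about its limits. It says the trial is not powered for patient-centered outcomes, that PPCs would need far more patients, and that driving pressure is a surrogate. A secondary endpoint need not be powered, and a condensed article may leave the PPC definition and analysis to the full protocol. All of this stands. Lack of power, the missing definition and the absence of a named PPC analysis in {20a} are not counted as faults here. The disclaimers do not remove the conflict, though. They show that the authors do not regard PPCs as evaluable, while the Abstract and {12} still list them.

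Some stronger readings are tempting, but the documents do not support them:

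- *The PPC count will be zero or close to it.* This depends on the share of early PPCs and on the definition, and neither is given. The Discussion treats lung ultrasound as a tool for detecting PPCs, and a postoperative scan is done, so an ultrasound-based definition could give a higher count.
- *The authors say PPCs cannot be evaluated because follow-up is short.* The Discussion gives patient numbers as its reason. The link to follow-up is drawn here from {13} and {30}.
- *The conclusion promises an answer on PPC risk.* It says only that results will show whether the strategy "has the potential of reducing the risk for postoperative pulmonary complications". That is hedged and can be read through the surrogate argument.
- *The registry entry is wrong.* It is not shown, so nothing can be said about it.

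**Conclusion.** The point holds as an internal contradiction with a practical consequence. Overall PPCs are a stated secondary outcome, the stated observation window cannot capture them, and the article elsewhere says that their occurrence could not be evaluated.

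On size, about 3 events would be expected in 60 patients at the article's 5% incidence with complete follow-up, and fewer within the recovery room if the same definition applies. How many fewer is unknown. For assumed shares of 50% to 5%, the chance of no event in the whole trial runs from 0.22 to 0.86. This range is illustrative. The conclusion does not depend on it, because a low count would be uninformative even with full follow-up.

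The primary endpoint, its sample size and its analysis are untouched. This should be corrected before results are reported, but it does not threaten the main question of the trial.

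**What to change.** **Change.**

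1. In the Abstract (Methods) and Outcomes {12}, replace overall PPCs with specified pulmonary events observed from arrival in the recovery room until discharge from it. The sponsor should name the event types.
2. State that these events are reported descriptively, as number and percentage per group, with no between-group claim about overall PPCs.
3. Add the restated outcome to the postoperative column of Table 1 with that time window.
4. Align the Discussion with it: say that later complications are not recorded as well as that patient numbers are too small, and let any conclusion on PPC risk rest only on driving pressure as a surrogate.

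The alternative is to remove the outcome through a documented amendment under {25}. Restating it is preferable. Recruitment began in March 2023, and deleting a listed outcome after that invites a question about selective reporting.

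**Cost.** A wording amendment, which {25} sends to the ethics committee for approval and then to the trial record. No procedure, sample size or primary analysis changes. The trial gives up a PPC claim that its design cannot support.
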